## Abstract

**Background:**

Smoking is the primary preventable risk factor for disease and premature mortality. It is highly addictive and cessation attempts are often unsuccessful. Incentive-based programmes may be an effective method to reach sustained abstinence. Individualisation of incentives based on personal characteristics yields potential to further increase the effectiveness of incentive-based programmes.

**Method:**

A randomised controlled trial among healthcare workers recruited through their employer and signed up for a group-based smoking cessation programme. The intervention under study is the provision of personalised incentives on validated smoking cessation at several time points after the smoking cessation programme. A total of 220 participants are required. Participants are randomised 1:1 into intervention (personalised incentives) or control (no incentives). All participants join the group-based programme. Incentives are provided on validated abstinence directly after the smoking cessation programme and after 3, 6 and 12 months.

Incentives are provided according to four schemes:

(1) Standard: total reward size €350, pay-out scheme: €50 (t=0), €50 (t=3 months), €50 (t=6 months) and €200 (t=12 months), (2) descending: total reward size €300, pay-out scheme: €150, €100, €50 and €0, (3) ascending: total reward size: €400, pay-out scheme: €0, €0, €50 and €350 and (4) deposit: total reward size €450, pay-out scheme: €50, €50, €150, €200; participants pay a €100 deposit, returned conditional on abstinence after 6 months.

Advice on which incentive scheme suits participants best is based on willingness to provide a deposit, readiness to quit, nicotine dependency and long-term or short-term reward preference. Participants are free to deviate from this advice. Abstinence is validated at each time point, with 15 months of total follow-up. The primary end point is validated abstinence at 12 months. Effectiveness will be determined by intention-to-treat analysis.

**Ethics and dissemination:**

The Erasmus MC Medical Ethics Committee decided that according to the Dutch Human Research Law (WMO), the protocol required no formal ethical approval. The results will be published in a peer-reviewed scientific journal and communicated to the participants.

**Trial registration number:**

Netherlands Trial Register NL7711.

Strengths and limitations of this studyThe PERSonalised Incentives for Supporting Tobacco cessation (PERSIST) trial has a unique hybrid design with a nudged choice embedded within a randomised trial and is the first of its kind to provide a personalised advice on the mode of providing incentives, which likely best fits individual participant characteristics.This trial furthermore addresses a knowledge gap regarding long-term effectiveness of incentive-based strategies beyond the actual intervention period.A focus on helping hospital employees quit smoking is essential given their exemplary role in promoting health.For logistical reasons, participants from the intervention and control arms may attend the same group sessions, potentially leading to spill-over effects.Due to the predicted sample size, it is not possible to include an additional intervention arm where incentives are provided but not personalised.

## Background

Smoking is the primary preventable risk factor for disease and premature mortality.^1^ Smoking is highly addictive and the vast majority of cessation attempts is unsuccessful.^2^ In 2017, 38% of smokers in the Netherlands attempted to quit for at least 24 hours.^3^ Several methods exist to increase the odds of quitting, such as nicotine replacement therapy (NRT),^4^ individual behavioural counselling^5^ and group-based smoking cessation programmes.^6^ However, despite the relative effectiveness of these approaches, in absolute numbers, the proportion of smokers who quit is still low.

A promising method to encourage smoking cessation is the provision of financial incentives upon validated abstinence. A recent Cochrane review found high-certainty evidence for increased smoking cessation rates at 6 or 12 months follow-up (risk ratio (RR)=1.49, 95% CI 1.28 to 1.73).^7^ Financial incentives make the desired behaviour—in this case smoking cessation—more attractive by rewarding it. Importantly, financial incentives provide a short-term reward for a behavioural change that would normally only provide rewards in the long term. Long-term rewards are often valued less compared with short-term rewards due to declining perceived values of a delayed reward, so-called delay discounting.^8^ Typically, people give disproportionally stronger relative weights to instantaneous rewards, so-called present bias,^9^ which gives a strong theoretical argument for providing short-term incentives for smoking cessation.

Incentive-based smoking cessation programmes have previously been implemented at the workplace.^10–12^ Recently, the ‘Continuous Abstinence Through Corporate Healthcare’ (CATCH) trial was carried out among 61 Dutch companies, randomising companies to group-based smoking cessation training for smoking employees with or without financial incentives to promote sustained cessation. Among those eligible to receive incentives (up to €350), the proportion of abstinent participants at 1-year follow-up was significantly higher compared with those assigned to group-based training alone (41% vs 26%).^13^

The effectiveness of incentives in promoting sustained smoking cessation depends on how and when rewards are provided. Traditionally, incentives have been tested according to a one-size-fits-all approach, using incentive size as a measure of anticipated effectiveness. A recent US trial comparing four different incentive programmes, however, showed that effectiveness is variable among different types and schemes of incentives.^10^ A deposit-based scheme, where participants commit their own money and return is conditional on validated abstinence, was unpopular but resulted in a significantly higher proportion of abstinent individuals compared with the reward-based incentive arm.^10^ Further analysis revealed associations between personal characteristics and acceptability and efficacy of incentive programmes.^14^ Both readiness-to-quit-smoking and low tendency to discount rewards were associated with increased effectiveness of both reward-based and deposit-based programmes. This suggests that personalisation of incentive programmes yields the potential to further increase the effectiveness of incentives to promote long-term abstinence.

Here we present the study protocol for the ‘Personalised Incentives for Supporting Tobacco Cessation’ (PERSIST) trial. The trial will be conducted among healthcare employees, for whom smoking cessation is particularly relevant as they may be expected to have an exemplary role. Moreover, in an attempt to work towards a smoke-free generation by 2040, the Dutch National Prevention Agreement requires university hospitals to be smoke free by mid-2020 and all healthcare facilities by 2025.

The aim of this study is to investigate whether personalised incentives in addition to a group-based smoking cessation programme will increase sustained smoking cessation among participants. This unique randomised controlled trial attempts to optimise the effectiveness of incentive programmes by providing personalised advice while leaving participants in full control to choose the incentive scheme of their choice. Our approach will further provide insight into which incentive scheme participants prefer and whether they can be nudged into the programme that most likely fits their personal characteristics best.

## Methods and analysis

### Objectives

The main objective is to evaluate the effectiveness of personalised incentives in combination with group-based training sessions provided in the work environment on sustained smoking abstinence among healthcare workers compared with group-based training sessions alone.

### Methods

The protocol follows the ‘Standard Protocol Items: Recommendations for Interventional Trials’ (SPIRIT) guidelines.^15^

### Trial design

The PERSIST trial is a randomised controlled non-blinded trial with two parallel arms.

#### Study setting

The trial will be implemented at Dutch healthcare institutions. The trial is primarily implemented at the Erasmus MC and is further being extended to Franciscus Gasthuis & Vlietland and Ikazia Hospital. Inclusion of other healthcare institutions in the greater Rotterdam area is ongoing.

#### Trial population and eligibility criteria

Employees are eligible if they are (1) aged 18 years or more, (2) employed at one of the participating healthcare institutions and (3) a daily smoker (ie, smoking at least one cigarette per day). Exclusion criteria are (1) only using e-cigarettes and (2) not being able to physically attend the group-based training sessions.

Participants are recruited through their employer. Information about the training and the PERSIST trial is spread through intranet, email, flyers and screensavers. In collaboration with the organisation responsible for the training (SineFuma, see the Interventions section), information sessions about the training and trial are organised.

### Interventions

Eligible participants are individually randomised 1:1 into a control arm, receiving no incentives, and an intervention arm, receiving personalised incentives. See figure 1 for a flowchart. Both arms participate in a group-based smoking cessation training provided by SineFuma, a company specialised in supporting smoking cessation (www.rookvrijookjij.nl). Groups consist of 8–16 participants and the training consists of seven sessions of approximately 90 min duration held over a period of 8 weeks. Participants in the intervention and control arms participate in the same training sessions for logistical reasons. Group-based training sessions will start as soon as at least eight people have signed up to avoid participants lose motivation due to long waiting times.

**Figure 1 F1:**
[figure not shown]
Flow diagram of participant inclusion plus outline of control and intervention conditions. *Participants are provided with an informed choice regarding the individualised incentive scheme based on: 1. Degree of tobacco dependence, 2. Readiness to quit and 3. Present-bias. Note: red arrows are conditional on sustained biochemically validated smoking cessation.

Group sessions are provided at locations within each of the participating healthcare institutions. The aim of the training is to quit smoking as a group: participants jointly quit smoking in the third session. The follow-on sessions then focus on supporting sustained cessation through the first few weeks following the quit attempt. The participants and coach discuss various types of NRT as part of the training. No NRT is provided in the trial but participants are free to use an NRT of their choice. During each session, exhaled carbon monoxide (CO) measurements (see the Outcomes section for more information) are used as a motivator to stay abstinent. The SineFuma group-based training is recognised as an efficient lifestyle intervention by the Dutch Government,^16^ and participation costs are reimbursed by basic insurance. As such, the control arm can be considered as usual care. If a portion of the costs are at the employee’s own expense through the deductible, employers have agreed to pay for the training.

#### Incentives

The difference between intervention and control conditions lies within the provision of incentives. Participants in the intervention arm who remain continuously abstinent following the joint quit attempt are eligible to receive incentives according to a fixed time schedule. Incentives are provided as vouchers representing monetary value. Vouchers can be spent at online web shops or on events such as a high tea in a local café or a night at a hotel and so on. Vouchers cannot be spent on tobacco products. The first incentive is provided directly after the group-based smoking cessation training, marking the moment from which participants have to remain abstinent independently.

In order to personalise incentives, four different incentive schemes are offered, which participants are free to choose from. Across the different schemes, the monetary value of the incentives varies over time, and the potential total financial reward differs. The schemes are as follows (see figure 1):

The standard scheme. Analogous to the CATCH trial,^13^ vouchers with a monetary value of €50, €50, €50 and €200 are offered on validated abstinence at t=0 month (ie, directly following the final smoking cessation training session), t=3 months, t=6 months and t=12 months, respectively. Hence, the maximum total amount of incentives that can be earned is €350.The descending scheme. Offer vouchers with a monetary value of €150, €100 and €50 on validated abstinence at t=0 month, t=3 months and t=6 months, respectively. No further incentives are provided at t=12 months. The maximum total amount of incentives is €300.The ascending scheme. Offer vouchers with a monetary value of €50 and €350 on validated abstinence t=6 months and t=12 months, respectively. No incentives are provided at t=0 and t=3 months. The maximum total amount of incentives is €400.The deposit-based scheme. Participants are asked to provide a €100 deposit at the beginning of the trial. The deposit scheme offers vouchers with a monetary value of €50 on validated abstinence at both t=0 and t=3 months. On validated abstinence at t=6 months, participants in this scheme will receive vouchers representing a monetary value of €150; in addition, their €100 deposit will be refunded. On validated abstinence, at t=12 months they will receive vouchers representing a monetary value of €200. Accordingly, the maximum total amount of incentives is €450, excluding the deposit refund. If one does not stay abstinent until 6 months after the last training session, the deposit will be donated to the Netherlands Lung Foundation.

In choosing the monetary amounts of incentives, we followed the general principle that the incentives should be large enough to motivate smoking cessation, but not too large either to avoid crowding out intrinsic motivation and to make scaling-up the trial prohibitively costly.^17^ The standard scheme is identical to the scheme in the CATCH trial.^18^ Given time discounting due to inflation and individual impatience, it seems natural to apply some compensation in the total potential gains to the descending and ascending schemes. For example, why would someone self-select into an ascending scheme with zero pay-out in the first 6 months if the total potential gain is the same as the descending scheme where one can cash-in €150—already after at baseline? Further, as deposit contracts have proven to be most effective among those who choose one,^10^ we aimed to make this scheme the most attractive by providing the largest total reward size.

The key aspect of the intervention is the personalisation of the incentives. The varying values over time and varying total reward sizes allow for differences in reward preferences. For example, those who prefer to earn money sooner can choose accordingly (descending scheme), however, in that case the maximum total amount rewarded will be lower, while patience is rewarded with a higher total amount (ascending scheme). Halpern *et al*^10^ showed that in the context of smoking cessation promotion at the workplace, deposit schemes are unpopular but very effective; therefore, the current deposit scheme is designed to be the most attractive by having the largest potential total reward.

In an attempt to maximise the effectiveness of incentive provision, participants receive automated advice regarding which scheme is most likely to fit their personal characteristics. This advice will be based on the following characteristics:

Degree of tobacco dependence. Based on the Fagerström Test for Nicotine Dependence.^19^ Fagerström score below 5=no/low nicotine dependence or Fagerström score of 5 or higher=nicotine dependent.Readiness-to-quit. Based on Prochaska Stage of Change.^20^ Preparation stage (readiness to quit within the next 30 days) or (pre)contemplation stage (ready to quit within the next 6 months or not ready to quit at all).^10 20^Present bias. Measured by temporal discounting magnitude based on the Kirby Scale.^21^ Temporal discounting refers to the phenomenon where future rewards are perceived as being worth less than an immediate reward.^21^ Based on a 27-item monetary choice questionnaire, those choosing more than 50% of the times the larger delayed rewards are classified as having delayed reward preference and those choosing less than 50% of the times the larger delayed rewards are classified as having present reward preference.^21 22^Willingness to pay a deposit, yes or no.

The first three factors have been associated with the effectiveness of smoking cessation interventions and with reaching sustained abstinence in reward-based programmes.^14^ The fourth factor is used as an indicator of acceptability of the deposit-based scheme, as deposit schemes are expected to be not only the most effective but also the least popular. The four factors are dichotomised into ‘positive’ or ‘negative’ values in order to advise participants. Positive values are associated with higher quit percentages, that is, being in a preparation stage, having low nicotine dependence and having a delayed reward preference. Negative values are associated with lower quit percentages, that is, being in a (pre)contemplation stage, being nicotine dependent and having an immediate reward preference.

A combination of three positive values leads to the ascending scheme, two positive values to the standard scheme and two or three negative values to the descending scheme (see table 1). Those willing to pay a deposit are automatically advised the deposit-based scheme. The rationale behind this is that those with the lowest scores are likely to experience the most trouble quitting, and hence arguably benefit most from higher rewards in the beginning. Those with a higher score might rather benefit from incentives as a motivator to remain abstinent, and thus receive higher rewards towards the end of the study period. Importantly, participants are, however, free to choose the scheme of their preference when entering the trial regardless of the advice they received.

**Table 1 T1:** Answer combinations and advised schemes

Degree of tobacco dependence*	Readiness-to-quit†	Present bias‡	Willing to pay a deposit	Scheme advice
<5	Ready to quit within the next 30 days	Delayed reward preference	No	Ascending
<5	Ready to quit within the next 30 days	Present reward preference	No	Standard
<5	Ready to quit in the next 6 months or not ready to quit	Delayed reward preference	No	Standard
<5	Ready to quit in the next 6 months or not ready to quit	Present reward preference	No	Descending
≥5	Ready to quit within the next 30 days	Delayed reward preference	No	Standard
≥5	Ready to quit within the next 30 days	Present reward preference	No	Descending
≥5	Ready to quit in the next 6 months or not ready to quit	Delayed reward preference	No	Descending
≥5	Ready to quit in the next 6 months or not ready to quit	Present reward preference	No	Descending
Any answer	Any answer	Any answer	Yes	Deposit

*Assessed via Fagerström score.

†Assessed via Prochaska state of change.

‡Assessed via Kirby discontinuity score.

As participants have freedom of choice over the incentive schemes, this is likely to result in a skewed distribution of participants over the schemes. However, this is not an issue in the current trial as the aim is to estimate the overall effect of personalised incentives compared with no incentives and not to estimate the discrete effects of the individual schemes. In fact, the current trial will provide information as to which schemes are most popular, how this relates to personal characteristics and whether participants may be nudged into the scheme that is assumed to best fit their personal characteristics.

### Outcomes

The primary outcome is CO-validated 12-month continuous abstinence from smoking (Russel’s Standard, RS12).^23^ The primary outcome is measured at t=12 months after the last group-based training. However, participants jointly quit smoking at the third training session which is approximately 1 month prior to the last training session. This 1-month gap between the joint smoking attempt and the start of our measurement allows participants to have a setback in smoking cessation while they are still in the training. From the end of the training (t=0 month) onwards, all participants are expected to be smoke free. Abstinence is assessed via self-reported abstinence and biochemically validated using expired air (CO) measurements. Self-reported abstinence assesses both point and continuous abstinence. Point prevalence is assessed by 7-day abstinence at each follow-up point and prolonged abstinence via the total continuous abstinence period.^23^ Self-reported abstinence is validated via assessment of expired air CO concentrations using a handheld monitor (PiCO Smokerlyzer, Bedfont Scientific, Kent, England). An exhaled-air CO reading of <10 ppm is considered indicative of abstinence.^23^ CO quantification is a reliable and non-invasive method to ascertain recent smoking and the preferred method in populations using NRT.^23^ In case of disagreement between self-reported abstinence and CO reading, abstinence is defined by the latter.

Secondary outcomes are smoking abstinence directly after the group-based smoking cessation training (t=0), and after 3 months (t=3), after 6 months (t=6) and after 15 months (t=15). The same methods and definitions to determine continuous abstinence are used for all outcomes.

Tertiary outcomes are the incremental cost-effectiveness ratio and the incremental cost-utility ratio, where the first is calculated using the total costs per quitter and the latter by the costs and self-reported quality of life (EurQol Five Dimensions).

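### With entry from one cigarette a day and a single CO cut-off of 10 ppm, some smoking may escape validation, and only the intervention arm is paid on validated abstinence

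*Protocol article*

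**What the plan says.** All references are to the protocol article.

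- **Entry** (Trial population and eligibility criteria): an eligible employee is "a daily smoker (ie, smoking at least one cigarette per day"). Exclusive e-cigarette users are excluded. No CO level is required at entry.
- **Criterion** (Outcomes): "An exhaled-air CO reading of <10 ppm is considered indicative of abstinence". The article names no second marker. It describes the method thus: "CO quantification is a reliable and non-invasive method to ascertain recent smoking and the preferred method in populations using NRT".
- **Conflict rule** (Outcomes): "In case of disagreement between self-reported abstinence and CO reading, abstinence is defined by the latter". The rule does not say in which direction the disagreement must run.
- **Self-report** (Outcomes): "Point prevalence is assessed by 7-day abstinence at each follow-up point and prolonged abstinence via the total continuous abstinence period".
- **Payment** (Interventions, Incentives): there is a "control arm, receiving no incentives, and an intervention arm, receiving personalised incentives". The condition is: "Participants in the intervention arm who remain continuously abstinent following the joint quit attempt are eligible to receive incentives according to a fixed time schedule". The 12-month voucher is €200 (standard), €0 (descending), €350 (ascending) or €200 (deposit).
- **Blinding** (Allocation): participants and outcome assessors know the allocation.
- **CO in the training** (text after Figure 1): "During each session, exhaled carbon monoxide (CO) measurements (see the Outcomes section for more information) are used as a motivator to stay abstinent". The joint quit is at the third session, so the first two readings precede it.

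**The concern.** Biochemical validation protects an unblinded, incentivised trial only if a person who smokes would fail the test. The plan combines a very low consumption floor with one fixed cut-off and gives no information on how many participants would already pass while smoking. Anyone in that position who denies smoking is counted as abstinent. The motive to do so is financial in one arm and absent in the other, so the resulting error need not be equal between arms. Where it is unequal in the expected direction, it favours the intervention on the primary endpoint.

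The term CO-validated would then promise more for these participants than the test delivers, and a reader of the results could not tell for how many. Data that bear on the question are collected or measured (baseline smoking behaviour, Fagerström score, session CO readings), but the article does not link any of them to it.

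**Working it through.** **1. The plan's own figure.** Inputs (Sample size): 50% v 30%, power 0.8, alpha 0.05 (taken as two-sided), 1:1. With pooled variance and no continuity correction:

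n per arm = [1.96 × √(2 × 0.40 × 0.60) + 0.8416 × √(0.50 × 0.50 + 0.30 × 0.70)]² / 0.20² = 93, so 186 in total.

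186 / 0.85 = 218.8, or 219; the plan states 220. The sample size reproduces and does not depend on this point.

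**2. Smoking that is denied and reads below 10 ppm.** Report and CO agree here, so the conflict rule never applies. Let

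- s = share of participants with pre-quit CO below 10 ppm (assumed 10–25%);
- a = share truly abstinent at 12 months (30%, the plan's control rate, taken for both arms so that there is no true effect);
- d = excess probability of a false claim in the paid arm among those in s who still smoke (assumed 10–20 points).

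Only people who are not abstinent can claim falsely, so inflation = s × (1 − a) × d.

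| s | 1 − a | d | inflation |
|---|---|---|---|
| 0.10 | 0.70 | 0.10 | 0.7 points |
| 0.25 | 0.70 | 0.20 | 3.5 points |

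With 110 per arm and 30% as the control rate, a normal-approximation test rejects at two-sided 5% in 5.1% of trials for 0.7 points and 8.6% for 3.5 points.

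Other assumptions move the result either way. With s = 5% and d = 25 points, it is 0.05 × 0.70 × 0.25 = 0.9 points (rejection 5.2%). With s = 20% and d = 50 points, it is 0.20 × 0.70 × 0.50 = 7.0 points (19.5%). The document supports no particular pair.

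**3. Smoking that is admitted and reads below 10 ppm.** Now report and CO disagree. Taken literally, the conflict rule makes CO decisive and counts the person as abstinent, in either arm. If a share q of non-abstainers is affected in both arms, with true rates of 50% and 30% and q = 20% (assumed):

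- intervention: 0.50 + 0.50 × 0.20 = 0.60;
- control: 0.30 + 0.70 × 0.20 = 0.44;
- difference: 0.16 instead of 0.20.

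Power at 93 per arm falls from 80% to 59%, and type I error stays at 5%. This route dilutes the effect.

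**4. Between visits.** The article describes CO as detecting recent smoking, so abstinence between visits can come only from self-report. That holds for every participant. What is particular to those who read below 10 ppm while smoking is that the check at the visit fails as well.

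**The case against.** The strongest reply is that the key premise is not in the document. The article gives no CO distribution and no share of light smokers, and it calls CO reliable. That stands: the size above is conditional on assumed inputs, and the fix is partly a way to learn them.

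A second reply is that CO overrides self-report, so the endpoint does not rest on what participants say. This stands only for admitted smoking, where the literal rule dilutes the effect (step 3). It does not reach denied smoking below the cut-off.

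Third, payment is made on validated abstinence, not on a bare claim, and the descending scheme pays nothing at 12 months. That weakens the motive for some participants but leaves the contrast between arms. The 15-month assessment, after payments end, is a partial check, but a false account of the earlier period can be carried forward.

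Fourth, the cut-off is referenced to a published standard, and sensitivity analyses commonly sit in a full protocol or analysis plan. This stands in that nothing here is numerically wrong and the absence of such analyses from an article is not itself a fault. What the article does fix is the combination of entry floor, cut-off and a conflict rule without direction.

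Two stronger readings are tempting. One is that the primary endpoint reduces to paid self-report and is biased by as much as 5 points (0.25 × 0.20). That omits the non-abstinent fraction and treats an assumed share as established. The other is that the analysis should simply be restricted to participants with a session 1–2 CO of at least 10 ppm. Allocation is released once the baseline questionnaires are complete, and Strengths and limitations says participants learn their status as early as possible. Those readings may therefore follow disclosure of allocation, and restricting on them could select on something the incentives had already changed.

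**Conclusion.** The point holds in a limited form. For participants who would read below 10 ppm while smoking, CO cannot refute a false claim, and the financial motive for such a claim exists in one arm only. Under the stated assumptions (10–25% of participants, 70% of them not abstinent, a 10–20 point excess of false claims) the arm difference is inflated by about 0.7–3.5 points, modest against the planned 20. Neither the share nor the excess can be taken from the document, and a literal use of the conflict rule for admitted smoking pulls the other way. The documents therefore do not support a conclusion that the trial is biased towards the intervention by any known amount, or that CO validation fails in general. They do support a low-cost clarification and two supporting analyses.

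**What to change.** 1. Keep the 10 ppm cut-off for the primary analysis.
2. In Outcomes, give the conflict rule a direction: CO can refute a claim of abstinence but cannot establish abstinence in someone who reports smoking.
3. Prespecify a supporting analysis of the primary endpoint by smoking intensity measured before randomisation, using the baseline smoking behaviour items or the Fagerström score. The planned subgroup at a Fagerström score of 5 can serve if it is also given this purpose. A CO reading may be used instead only if taken before allocation is disclosed. A larger effect among lighter smokers may be genuine or may reflect misreporting, so the estimate in heavier smokers is the more informative one here.
4. Prespecify a second supporting analysis with one lower CO cut-off, fixed in advance and applied to the recorded ppm values.
5. If the training provider can supply the session 1–2 readings, record them to describe how many participants read below 10 ppm while smoking, and note that they may post-date allocation. The article does not say whether they are stored.

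The cost is a sentence in the endpoint definition, retention of ppm values and two supporting analyses. The downsides are lower precision in those analyses and, with a lower cut-off, a few true abstainers misclassified as smoking.
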